## Abstract

**Background:**

The anxiety and their related disorders (AD) are the most common of all mental health conditions, and affect approximately 20% of pregnant and postpartum people. They are associated with significant distress and life interference for sufferers, as well as negative consequences for fetal and infant development. At present, little if any routine screening for prenatal AD is being conducted and data regarding the most effective tools to screen for these disorders is lacking. The majority of screening studies suffer from methodological difficulties which undermine the confidence needed to recommend measures for population distribution. The primary purpose of this research is to identify the most accurate self-report tool(s) to screen for perinatal AD.

**Methods:**

A large, prospective cohort of pregnant people (*N* = 1,000) is being recruited proportionally across health service delivery regions in British Columbia (BC). The screening accuracy of a broad range of perinatal AD self-report measures are being assessed using gold standard methodology. Consenting individuals are administered online questionnaires followed by a semi-structured diagnostic interview between 16- and 36-weeks’ gestation, and again between 6 and 20 weeks postpartum. Questionnaires include all screening measures, measures of sleep and unpaid family work, and questions pertaining to demographic and reproductive history, COVID-19, gender role burden, and mental health treatment utilization. Interviews assess all current anxiety disorders, as well as obsessive–compulsive disorder, and posttraumatic stress disorder.

**Discussion:**

This research is in response to an urgent demand for accurate perinatal AD screening tools based on high quality evidence. AD among perinatal people often go unidentified and untreated, resulting in continued suffering and life impairment. Findings from this research will inform healthcare providers, policymakers, and scientists, about the most effective approach to screening for anxiety and related disorders in pregnancy in the postpartum period.

## Introduction

For many health conditions, screening is the first step in a pathway to effective, and in some cases lifesaving, interventions [1–3]. It allows for population level early disease detection thereby identifying those in need of further assessment and ultimately treatment. Further, screening provides significant cost savings [4–8] by ensuring that only those who require more time and labour-intensive diagnostic assessments are offered them [4, 8–10]. Although screening for mental health conditions has been shown to lead to improved mental health even in the absence of a clear pathway to treatment [11, 12], there are still several gaps in screening for mental health conditions in Canada, particularly in the perinatal period [13].

The current edition of the Diagnostic and Statistical Manual of Mental Disorders (DSM-5) [14] includes ten anxiety disorders and several anxiety-related disorders (AD). For the purposes of this research, we have defined AD to include all DSM-5 anxiety disorders as well as two anxiety-related disorders: posttraumatic stress disorder (PTSD) and obsessive–compulsive disorder (OCD) [14]. The AD affect one in five pregnant and postpartum people [15], and are of high importance for perinatal people both due to the fact that they are highly prevalent, but also because they are associated with a range of negative reproductive health outcomes [15–17]. These include: obstetrical (e.g., miscarriage, low birth weight, preterm delivery) [16, 18–21]; fetal and infant (e.g., impaired self-regulation and motor development, and an increased risk for attention-deficit/hyperactivity disorder) [16, 22–28]; and the birthing parent (e.g., postpartum depression, reduced employment capacity, unemployment, and decreased social, emotional and physical functioning) [16, 17, 29–35]. The AD are also associated with significant health care costs and increased health care service utilization [36–39].

Routine screening for perinatal depression is employed in many parts of the world [40–42]. This has been made possible through the availability of screening tools for perinatal depression of high and well-established accuracy [43, 44]. Despite the fact that, among perinatal people, AD are significantly more common that perinatal depression (21% for perinatal AD, and approximately 6% for perinatal depression) [15, 45] screening for these conditions is almost non-existent [4]. This is largely the result of a lack of identifiable screening tools with established and high accuracy [46]. Numerous self-report screening tools for perinatal AD have been developed and to some extent evaluated [47]. More than one may, in fact, prove to be highly accurate. However, assessments of their accuracy have been burdened by methodological weaknesses of sufficient magnitude such that, at present, no screening tool for perinatal AD can be recommended with confidence [48].

What makes the establishment of broadly disseminated screening for perinatal AD so appealing is the following. First, perinatal people are highly accepting of screening programs, but tend not to discuss their mental health difficulties unless asked about them [4, 49]. Consequently, without screening, perinatal AD will often go undetected [50]. Second is the recent increase in the availability and acceptability of highly effective, evidence-based treatments for perinatal AD. Specifically, cognitive behaviour therapy (CBT), a form of talk therapy, is the treatment of choice for many anxiety-related conditions. Randomized controlled trials comparing CBT with medication approaches have found that CBT is safe and equal or superior to medication [51–53], and a recent systematic review found CBT to effective for perinatal populations [54]. Historically, access to CBT has been limited and not broadly publicly funded due to the fact that it is time-consuming and expensive [55–57]. More recently, however, CBT has become increasingly available in self-administered and online formats, greatly improving accessibility [58, 59], without any loss in effectiveness [60, 61]. Accordingly, when screening leads to appropriate treatment, positive outcomes are highly likely.

The need for accurate, evidence-based screening tools is now more critical in light of recent urgent calls by various healthcare agencies for perinatal AD screening, and guidance regarding screening tool selection. These include the Perinatal Services BC [62], the American College of Obstetricians and Gynecologists [63], MGH Centre for Women’s Mental Health [64].

As population-wide administration of screening programs is a large, expensive undertaking, and the primary determinant of who will receive more costly diagnostic assessments, ensuring that resources are well spent is critical and can only be achieved when valid screening tools are employed. To be valid, screening tools must demonstrate a high level of accuracy when compared with gold standard diagnostic assessments. For this to occur, very specific research methodology is required. The Cochrane Screening & Diagnostic Tests Methods Group recommends the Quality of Diagnostic Accuracy Studies (QUADAS-2) [48, 65] as the criteria of choice for assessing studies of diagnostic accuracy [65–67]. QUADAS-2 criteria were also formally accepted by the Australian National Health and Medical Research Councils [4]. The QUADAS-2 criteria are outlined below, with some language adjusted to reflect requirements when screening for mental health difficulties among perinatal people. Specifically, assessments of perinatal AD screening tools should:employ a representative or unselected general sample of pregnant and/or postpartum people;assess screening tool(s) against gold standard diagnostic assessments (for mental health conditions, semi-structured diagnostic interview);assess, minimally, the core AD with or without OCD and PTSD;ensure diagnostic assessments are conducted blind to screening test(s) results;ensure appropriate timing between screening and diagnostic assessment; andpower to adequately detect the above metrics.

Beyond the above methodological criteria needed to correctly assess screening tool accuracy, studies assessing screening tool accuracy must also report screening tool metrics sufficient to allow an assessment of accuracy. Specifically, studies should measure diagnostic accuracy, reporting minimally, area under the curve (AUC), and sensitivity and specificity at specified cut-offs (both with 95% Confidence Limits). The AUC, sensitivity and specificity should also be reported independently of other disorders (e.g., depression). To merit broad dissemination, screening tool metrics should meet a certain threshold of accuracy. In our opinion, the empirical literature supports the following minimum criteria be met for a screening tool to be deemed “sufficiently accurate” as to merit implementation [68–70]:An AUC of ≥ 0.8 (≥ 0.8 is generally considered excellent) [71].A Youden’s “*J*” index (Youden 1950) of ≥ 0.5 (i.e., when sensitivity = 0.75, specificity ≥ 0.75).A negative predictive value (NPV) ≥ 0.8.A positive likelihood ratio (LR +) of ≥ 4.0. A LR + of 4.0 means that with a positive test result, the probability the person has the disease increases 25% over pre-test probability [72].

The overwhelming consensus from the perinatal AD screening literature, and experts in the field, is that the evidence meets neither: (a) the necessary methodological criteria described above, nor (b) the threshold of “sufficiently accurate” outcome metrics. Consequently, the evidence base remains inadequate to enable clear recommendations regarding optimal screening practice [4, 6]. Although a large number of potential AD screening tools have been evaluated within perinatal populations and several reviews of this literature have been published [4, 6, 40, 73, 74], all published studies are hampered by one or more important methodological weakness. These include: failing to assess the full composite of the AD; reporting insufficient metrics [75–78]; reporting accuracy for depression and AD combined [75, 77, 78]; employing selected rather than representative or unselected samples (e.g., specific groups of perinatal people are excluded such as those with depression or medical risk in pregnancy) and administering diagnostic interviews prior to the administration of screening tools, influencing screening tool completion [79–84].

To our knowledge, only two studies of perinatal AD screening tool accuracy have been conducted using full gold standard methodology [5, 46, 85]. Data from one (reported across two publications) provides support for the Edinburgh Perinatal Depression Scale – Anxiety Items (EPDS-3A) and the Matthey Generic Mood Question (MGMQ) [5, 85]. However, insufficient information regarding screening tool accuracy was reported. Consequently, while this study can be used to support the inclusion of the EPDS-3-A and the MGMQ in future evaluations, it cannot be used to draw firm conclusions regarding their accuracy. Further, our own study of postpartum people, some, albeit weak, support for the EPDS-3-A and the General Anxiety Disorder – 7 (GAD-7) was found [46].

Although existing studies’ findings do help to select tools deserving of further investigation, they fall far short of identifying an accurate and reliable, much less an optimal, screening tool for perinatal AD. Despite an urgent public health need, to date, no accurate perinatal AD screening tools have been identified. The proposed research aims to fill this gap.

### Objectives

The core objective of this research is to identify one or more accurate screening tools to detect perinatal AD. To this end, we will:Assess the accuracy of a range of screening tools for perinatal AD as a whole and individually. Specifically, we will report the full composite of screening tool metrics for each evaluated measure:i)at each assessment point (prenatal and postpartum);ii)for the core DSM-5 anxiety disorders alone, and including OCD and PTSD;iii)for each of the individual AD; andiv)across parity (parity = 0, parity ≥ 1) and major ethnic groups.Based on the above, we will report the most accurate screening tool for the AD as a group, and for each individual AD.

Secondary and exploratory study objectives:Document the prevalence of perinatal AD in pregnancy and the postpartum. As this study requires an unselected/representative sample of perinatal people from within a specified geographical region, it provides the opportunity for us to document prevalence.Explore relationships between participant demographic characteristics (e.g., age, relationship status, race/ethnicity, household income, income needs, education, employment status, geographical area of residence), identity (gender, sexual orientation), experiences with discrimination (e.g., race, social class, religion, weight/body size, chronic illness, history of substance use), and sleep with AD.Assess perinatal people’s experience with mental health assessment and treatment seeking and utilization. Among participants who reported symptoms meeting criteria for one or more AD, we will assess assessment and treatment seeking as well as any barriers experienced (e.g., cost, location, race or culture, time, etc.). Among those who received an assessment or treatment, we will ask about the nature, duration, and costs associated with any assessments or treatment received, as well as diagnoses obtained, and practitioner type.Assess the relationship between unpaid domestic labour (i.e., household chores and childcare responsibilities) and mental health and relationship satisfaction. Specifically, we will assess the overall burden (i.e., quantity), perceptions of fairness, and gender distribution of unpaid domestic labour with respect to mental health and relationship satisfaction prenatally and postpartum.

## Methods

### Study design

The current study employs a prospective cohort design.

### Inclusion criteria

All pregnant individuals, living in the province of British Columbia (BC), over the age of 18 and able to speak and read English at a level sufficient to complete the study questionnaires and interviews are eligible to participate in this research.

### Recruitment

We are employing a range of recruitment approaches with an emphasis on internet-based strategies, specifically, paid social media advertisements utilized for general population recruitment throughout the province. This method is supplemented with unpaid internet-based community recruitment to target rural, diverse, and marginalized communities. This entails the posting of study advertisements and posters on our lab social media sites (e.g., Facebook, Instagram, Twitter) and other online settings frequented by pregnant people in BC (e.g., pregnancy-related blogs, Facebook or Instagram pages, and websites).

Diverse sample recruitment is being carried out via partnerships with midwifery clinics, family physicians’ and obstetricians’ offices, and community centres and other community organizations. This recruitment consists of an introductory phone call or email to the agency, followed by an email including study information, study pamphlet, and posters to print or share with clients and the community. This form of recruitment is used to focus efforts on collecting a diverse, proportionally representative sample of the birthing population in the province and allows us to target additional populations that would otherwise not be reached through social media.

### Sample representativeness

To achieve a sampling frame that is 80–90% representative of the population of English-speaking birthing people in BC, participants are being recruited proportionately across BC’s five Health Authorities. To further enhance sample representativeness, sample characteristics (e.g., age, parity, education, geographical area) are tracked and compared to the BC perinatal database population data for the timeframe of recruitment. As needed, enhanced recruitment and sample weighting will be used to adjust for differences. All recruitment materials are inclusive of minorities and gender-diverse people.

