#### Consent

Consent for this project is provided electronically at the time of enrollment. Interested individuals are able to access the study intake form from advertisements and are able to follow links to the consent form and eligibility questionnaire. Upon providing consent, participants are then able to download and save a PDF copy of the consent form for their personal records. By consenting to participate, participants are also consenting to complete the study interviews. Participants are informed of limits to confidentiality (i.e., urgent risk of harm to oneself, or harm coming to a child) in the consent form and at the beginning of each interview.

Consent for recording the interviews (for the purpose of assessing inter-rater reliability) is requested verbally at the beginning of each interview.

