## Discussion

It is now evident that perinatal AD are highly prevalent (1 in 5 perinatal people), impairing, distressing with potential negative effects for the developing fetus and infant [15–17]. Detection, prevention, and treatment are highly important to mitigating these consequences. Accurate and reliable screening is a critical first step to identifying those at risk of, or currently suffering from, these disorders. Despite calls for implementation [62, 64], perinatal AD screening is rarely conducted. This is in large part because the current published literature fails to provide sufficient empirical support for any instrument. Although much research evaluating perinatal AD screening tools has been conducted, it has been hampered by methodological shortcomings of such magnitude that no available screening tool can justifiably be recommended for widespread implementation.

For these reasons we have undertaken a large-scale study of the accuracy of a broad range of potential perinatal AD screening tools. Our objective is to identify, employing gold standard methodology, one or more accurate and reliable measures. We have sought to overcome the methodological shortcomings of previous research so that our findings can be justifiably used to make practice and policy decisions. Population-based administration of screening tools is expensive to implement and is unlikely to be undertaken without strong evidence that the screening tool(s) employed will in fact correctly identify those experiencing the disorders being screened for.

To our knowledge, this will be the first study in which all gold standard methodology has been employed. Specifically, in this research:all of the core anxiety disorders and additional anxiety-related disorders are assessed;gold standard, diagnostic interviews are administered;diagnostic assessments are conducted blind to screening tool results;DSM-5 diagnostic criteria are employed;an unselected/representative sample of pregnant and postpartum people is being sought;screening accuracy is assessed in both pregnancy and the postpartum; anddiagnostic interviews are administered within two to six weeks of completion of screening tools.

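### An opt-in volunteer sample is described as an 80–90% representative sampling frame, and the prevalence, PPV and NPV results inherit that unsupported claim

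*Protocol article*

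**What the plan says.** The Sample representativeness section states its goal as "To achieve a sampling frame that is 80–90% representative of the population of English-speaking birthing people in BC". The means are that "participants are being recruited proportionately across BC’s five Health Authorities" and that "sample characteristics (e.g., age, parity, education, geographical area) are tracked and compared to the BC perinatal database population data", with extra recruitment and weighting where differences appear.

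The Recruitment section names as its main route "paid social media advertisements utilized for general population recruitment throughout the province", supplemented by unpaid online posts. Clinics and community organisations receive study information, a pamphlet and "posters to print or share with clients and the community". On entry, the Consent section says: "Interested individuals are able to access the study intake form from advertisements". The article describes no list of pregnancies or births, no random draw and no consecutive enrolment.

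The Discussion lists among its gold-standard features that "an unselected/representative sample of pregnant and postpartum people is being sought". Under Objectives the same property is the reason given for a secondary objective: "it provides the opportunity for us to document prevalence". Sample size estimation attaches a 1.5-point margin of error to the prevalence of a 3% condition, and the Discussion also promises point prevalence and postpartum incidence. The data analysis plan will report PPV, NPV and percent correct classification.

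**The concern.** A sampling frame is a list, or its equivalent, from which people are drawn with known chances. With opt-in recruitment there is no denominator of people approached, so no participation rate can be computed. A percentage of representativeness then has no defined meaning.

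Matching the province by region and weighting to age, parity, education and area corrects imbalance in those variables. It corrects selection on AD only if, within the weighting strata, people with and without AD are equally likely to join. The article does not state this condition, and none of the tracked variables it names is a mental-health variable.

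What is at stake is the prevalence objective, the meaning of its confidence interval, and the measures that depend on AD frequency. A confidence interval at n = 1,000 describes sampling error only and says nothing about who volunteered.

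**Working it through.** **The plan's own figures.** The 80–90% cannot be reproduced, because no numerator, denominator or criterion is given. The prevalence margin can be checked: 1.96 × √(0.03 × 0.97 / 1000) = 1.06 points. The stated 1.5 points is therefore conservative (it corresponds to n of about 497), but it covers sampling error only.

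**Inputs.** True AD prevalence p = 20% (Abstract, and one in five in the Introduction); n = 1,000 per time point (Sample size estimation). The illustrative tool has sensitivity 0.75 and specificity 0.8125, so LR+ = 0.75 / 0.1875 = 4.0, the article's minimum, and LR− = 0.25 / 0.8125 = 0.308. The relative chance of joining with AD versus without, r, is not in the documents. It is an assumption, taken to be the same in every weighting stratum.

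**Formulas.**
- Observed prevalence = r·p / (r·p + 1 − p)
- Observed odds = 0.25·r, so PPV odds = 4.0 × 0.25·r = r and PPV = r / (1 + r)
- NPV = 1 / (1 + 0.308 × 0.25·r)

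| r (assumed) | Observed prevalence | Shift (points) | PPV | NPV |
|---|---|---|---|---|
| 0.75 | 15.8% | −4.2 | 43% | 0.945 |
| 1.0 | 20.0% | 0 | 50% | 0.93 |
| 1.25 | 23.8% | +3.8 | 56% | 0.91 |
| 1.5 | 27.3% | +7.3 | 60% | 0.90 |
| 2.0 | 33.3% | +13.3 | 67% | 0.87 |

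The sampling margin at 20% is 1.96 × √(0.2 × 0.8 / 1000) = 2.5 points. Upward bias equals that margin at r = (0.2248 × 0.8) / (0.2 × 0.7752), about 1.16. For a 3% condition, bias equals the stated 1.5-point margin at r = (0.045 × 0.97) / (0.03 × 0.955), about 1.52.

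Percent correct for this tool is 0.8125 − 0.0625 × prevalence. It depends on prevalence but moves little: 80.3% at r = 0.75, 80.0% at r = 1 and 79.2% at r = 2.

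**What weighting does.** Take two demographic strata (assumed values) with population shares 0.4 and 0.6, true prevalences 25% and 16.67%, sample shares 0.6 and 0.4, and r = 1.5 in both. True prevalence is 20.0%. Stratum estimates become 0.375 / 1.125 = 33.3% and 0.250 / 1.083 = 23.1%. Unweighted: 0.6 × 33.3 + 0.4 × 23.1 = 29.2%. With exact demographic weights: 0.4 × 33.3 + 0.6 × 23.1 = 27.2%. Weighting removes the demographic imbalance and leaves the selection on AD.

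**Measures that do not move.** Sensitivity is computed among people with AD and specificity among people without. Changing only the ratio of the two groups leaves both unchanged, and with them AUC, J and the likelihood ratios.

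**The case against.** The strongest reply is that the study exists to measure screening accuracy, and its core measures are untouched by selection on AD status alone. This stands. A reader might infer that self-selection undermines the primary comparison of tools; the documents give no support for that. Nor does the illustration change whether a tool would be accepted: PPV is not among the article's sufficiency criteria, and NPV, which is, stays above 0.8 throughout the range.

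A second reply is that the bias is hypothetical. This also stands in part. The article does not say what the advertisements tell readers, so one cannot assert that people with AD are drawn to them, or that prevalence will be overestimated. Near r = 1 the bias is smaller than the sampling margin. The point is that the plan claims a property that would rule the bias out, without having it.

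Third, the mitigation is broader than four variables. The list of characteristics is given as examples, enhanced recruitment is planned, and clinic and community partnerships reach people whom social media would miss. These help with coverage, but each route is still opt-in, and none addresses AD-related participation.

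Fourth, some wording states aims rather than results, and the eligibility criteria are broad, so the sample is unselected in the narrow sense that few people are excluded. Prevalence, however, needs representative participation, and the Objectives rest it on exactly that property.

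Finally, readers can compute PPV and NPV at any prevalence from the reported sensitivity and specificity. That is true, and it makes this part of the fix a modest addition.

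**Conclusion.** The point holds in a limited form. The recruitment described yields a volunteer sample with regional balance. The sampling-frame wording, the undefined 80–90% and the representative label credit the design with a property it lacks. The results exposed are prevalence with its margin of error and, through AD frequency, PPV, NPV and (slightly) percent correct classification.

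If true prevalence is 20% and relative participation lies between 0.75 and 2.0 within weighting strata, observed prevalence lies between 15.8% and 33.3%. That is a shift of 4 to 13 points against a sampling margin of about 2.5. PPV at LR+ 4.0 lies between 43% and 67% instead of 50%. The participation values are assumptions; the documents fix neither size nor direction.

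The Discussion also mentions over-sampling people with specific AD. That is a separate matter, and this point does not depend on it.

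**What to change.** - In Objectives, Sample representativeness and the Discussion, drop the 80–90% figure and the representative label. Describe a volunteer sample balanced by Health Authority and compared with provincial data.
- Report AD frequency as a cohort estimate, with a sensitivity table over relative participation, for example 0.75 to 2.0 and including 1.0.
- In Sample size estimation, state that the prevalence margin covers sampling error only.
- Report PPV and NPV at fixed prevalences, for example 10%, 20% and 30%, in addition to the sample frequency.

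The cost is rewording and two small tables. No new data or change in recruitment is needed, so it can be done with recruitment already about 60% complete. The downside is a weaker prevalence claim.
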